## Abstract

**Background:**

Normal levels of plasma antithrombin (AT) activity might decrease heparin requirements to achieve an adequate level of anticoagulation during treatment with extracorporeal membrane oxygenation (ECMO). Acquired AT deficiency during ECMO is common, but formal recommendations on target, timing, and rate of AT supplementation are lacking. Thus, we conceived a pilot trial to evaluate the feasibility and safety of prolonged AT supplementation in patients requiring veno-venous ECMO for respiratory failure.

**Methods:**

Grifols Antithrombin Research Awards (GATRA) is a prospective, randomized, single blinded, multicenter, controlled two-arm trial. Patients undergoing veno-venous ECMO will be randomized to either receive AT supplementation to maintain a functional AT level between 80 and 120% (AT supplementation group) or not (control group) for the entire ECMO course. In both study groups, anticoagulation will be provided with unfractionated heparin following a standardized protocol. The primary endpoint will be the dose of heparin required to maintain the ratio of activated partial thromboplastin time between 1.5 and 2. Secondary endpoints will be the adequacy of anticoagulation and the incidence of hemorrhagic and thrombotic complications.

**Discussion:**

GATRA is a pilot trial that will test the efficacy of a protocol of AT supplementation in decreasing the heparin dose and improving anticoagulation adequacy during ECMO. If positive, it might provide the basis for a future larger trial aimed at verifying the impact of AT supplementation on a composite outcome endpoint including hemorrhagic events, transfusion requirements, and mortality.

**Trial registration:**

ClinicalTrials.gov, NCT03208270. Registered on 5 July 2017.

**Electronic supplementary material:**

The online version of this article (10.1186/s13063-019-3386-4) contains supplementary material, which is available to authorized users.

## Background

Extracorporeal membrane oxygenation (ECMO) is a temporary life support method for patients with severe acute respiratory failure refractory to conventional treatment, and its use is continuously increasing worldwide [1]. Since exposure of blood to the non-biologic surface of the extracorporeal circuit induces a pro-thrombotic state and an inflammatory response, the use of ECMO necessitates the maintenance of hemostatic balance to minimize the risk of both hemorrhagic and thrombotic complications [2]. Consequently, to avoid clotting in the extracorporeal circuit and in the patient, anticoagulation is necessary, but it increases the risk of bleeding [3]. A recent retrospective analysis on more than 2000 patients reported bleeding and thrombotic complications with a frequency of up to 45% and 60%, respectively, with major impact on outcome [4].

Anticoagulation management during ECMO is usually based on continuous infusion of unfractionated heparin [5, 6]. The heparin effect is strictly dependent on antithrombin (AT) activity in plasma [7, 8]. Acquired AT deficiency during ECMO is common and multifactorial [9]: possible mechanisms include consumption due to activated coagulation and long-term anticoagulation, but also impaired synthesis, degradation by elastase from activated neutrophils, and disseminated intravascular coagulation. AT deficiency contributes to heparin resistance, with resulting difficulty in achieving therapeutic anticoagulation and increased heparin dose [7]. Theoretically, normalization of AT levels should decrease heparin requirements to achieve a proper anticoagulation target [9]. This may have a relevant clinical impact because risk of bleeding during ECMO is reasonably associated with higher heparin dosage, and a better control of anticoagulation may improve patients’ outcome [10]. However, formal recommendations on target, timing, and rate of AT supplementation during ECMO are lacking.

Given this lack of current knowledge, we designed a prospective randomized controlled clinical trial to evaluate the effects of a protocol of AT supplementation to achieve and maintain a normal AT activity on heparin dose, level of anticoagulation, bleeding, and thrombotic complications in adult patients undergoing ECMO for respiratory failure.

The results of this study will clarify some of the unanswered issues on AT supplementation during ECMO and will eventually provide the basis for a subsequent larger study on outcome.

## Methods

### Study design

The Grifols Antithrombin Research Awards (GATRA) study is a pilot, prospective, randomized, single blinded, multicenter, controlled two-arm trial that will be performed on adult patients undergoing veno-venous ECMO for severe respiratory failure. The study will be conducted in adherence to the principles of the World Medical Association’s Declaration of Helsinki and in accordance with the Medical Research Involving Human Subjects Act (WMO). The Ethics Committee of the coordinating center (Comitato Etico Milano Area B) approved the protocol on April 18, 2017 (Version 1.6.7 - April 4, 2017), and approval of the local Ethics Committees will be required before starting the trial in the participating centers. The study was authorized by AIFA (Agenzia Italiana del Farmaco) on April 11, 2017 (EudraCT number 2016-004534-23) and registered at www.ClinicalTrials.gov with code NCT03208270. Informed consent to participate in the clinical trial will be obtained, and information on the clinical trial will be given to each patient. If the patient is not capable of giving informed consent at the time of enrollment, a deferred consent will be given. The informed consent will be sought by the investigator from the patient, and the information about the study will be given to the patient or his/her legally designated representative as soon as possible. If the patient does not consent to the study, he/she will be informed of the right to object to the use of data obtained from the clinical trial. The Standard Protocol Items: Recommendations for Interventional Trials (SPIRIT) checklist is provided in Additional file 1, and the SPIRIT figure is included in the main body of the manuscript (Fig. 1).

**Fig. 1 Fig1:**
[figure not shown]
Intervention and assessment schedule

### Setting

The GATRA trial will be performed in the intensive care units (ICUs) of Italian ECMO referral centers. The coordinating center will be Fondazione IRCCS Ca′ Granda OspedaleMaggiore Policlinico in Milan, Italy.

### Study population

Consecutive adult patients admitted to the participating centers requiring veno-venous ECMO as a support for respiratory failure will be enrolled in the study. Exclusion criteria will be pre-existing heparin-induced thrombocytopenia or other contraindications to heparin use (namely high risk of bleeding after major surgery prompting the decision to start ECMO without systemic anticoagulation). The Consolidated Standards of Reporting Trials (CONSORT) diagram of the GATRA trial is presented in Fig. 2.

**Fig. 2 Fig2:**
[figure not shown]
CONSORT flow diagram

### Randomization

As soon as the clinical decision to initiate ECMO is made, the patient will be enrolled in the study. Patients will be block randomized per center through an online automatic centralized and computerized system to one of the two groups (1:1 ratio): AT supplementation group or control group.

### Interventions

#### Antithrombin supplementation group

Patients randomized to the AT supplementation group will receive supplementation of AT concentrate to maintain a functional AT level between 80 and 120%. The AT level will be measured prior to ECMO start and then once daily and supplementation adjusted accordingly. In the study group, AT concentrate supplementation will be interrupted when AT levels exceeds 120% and resumed as soon as the levels drop below 80%. The protocol for AT supplementation is illustrated in Fig. 3.

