### Development of the protocol for AT supplementation: practical and operational issues

Since dosing recommendations are not provided for acquired AT deficiency, the protocol for AT supplementation was developed following manufacturer recommendations for hereditary deficiency. Supplementation dosing is based on patient body weight and the difference between the actual and the desired AT activity. A level of AT activity corresponding to the normal range (80–120%) was chosen as the target for supplementation. The calculated dose was rounded up to the nearest vial size, and dose tiers were created using ranges of AT activity to minimize bedside calculations. The protocol mandates, for patients in the AT supplementation group, the administration of a loading dose of AT upon ECMO cannulation. As the level of AT activity before ECMO start was expected not to be available for most patients, the loading dose is based solely on the patient body weight. Subsequent dose adjustments are based on the patient body weight and the plasma AT activity, which must be measured daily. Patients with a plasma AT activity between 80 and 120% will receive a maintenance dose, which will be increased by 1000 IU if the plasma AT activity is lower than 80%. Observational studies suggest that intermittent administration of AT is less effective than continuous infusion in correcting AT deficiency; moreover, rapid AT binding to heparin complexes after bolus administration could theoretically increase the risk for bleeding. Based on the clinical experience of our and other ECMO centers [26, 27], administration of AT via an extended infusion decreases heparin rate modifications and avoids AT levels fluctuations, without increasing the risk of major bleeding. Therefore, the protocol prescribes AT administration by extended infusion both for loading and maintenance doses.

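### After antithrombin (AT) is held above 120%, the article's two dosing descriptions give opposite instructions for a daily level of 80–120%

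*Protocol article*

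**What the plan says.** The protocol article describes AT dosing in the intervention arm in two places.

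- **Methods, Antithrombin supplementation group.** The aim is "supplementation of AT concentrate to maintain a functional AT level between 80 and 120" per cent. On monitoring: "The AT level will be measured prior to ECMO start and then once daily and supplementation adjusted accordingly". On stopping and restarting: "AT concentrate supplementation will be interrupted when AT levels exceeds 120% and resumed as soon as the levels drop below 80" per cent. For the algorithm the reader is sent to a figure: "The protocol for AT supplementation is illustrated in Fig. 3". That figure is not reproduced in the text available for this review, which is not a fault of the plan.
- **Discussion, Development of the protocol for AT supplementation.** The daily rule is: "Subsequent dose adjustments are based on the patient body weight and the plasma AT activity, which must be measured daily". For the band itself: "Patients with a plasma AT activity between 80 and 120% will receive a maintenance dose, which will be increased by 1000 IU" when activity is lower than 80%. This text does not mention a hold or a level above 120%.

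The primary endpoint is heparin per kilogram per hour over the whole infusion (Primary endpoint). The trial plans 20 patients per arm (Sample size).

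**The concern.** The AT regimen is the intervention under test. If its written description gives two answers for the same patient on the same day, the regimen is not fully defined, and a treating team could follow either text in good faith.

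Three stated purposes depend on what is actually given: the contrast in heparin dose, the assessment of whether normal AT levels can be sustained, and the random-effect models relating AT dosage to heparin dosage (Discussion; Proposal for analysis). With 20 patients per arm, a handful of patients handled differently would be a visible share of the arm. Whether there are such patients is a separate question, taken up in the verdict.

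**Working it through.** No figure in the plan depends on this point, so there is nothing to reproduce numerically. The check writes each text as a rule and compares the two.

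**Inputs**

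1. Methods rule: hold above 120%; once held, restart below 80%. It depends on today's level and on whether AT is running or on hold.
2. Discussion rule: maintenance dose at 80–120%; that dose plus 1000 IU below 80%. It depends on body weight and today's level. Hold status is not named.
3. AT is measured once daily, so each decision uses one daily value.

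**Comparison at test levels**

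| State before today's value | Today's AT level | Methods rule | Discussion rule | Compatible? |
|---|---|---|---|---|
| Running | 70%, 79% | AT given | Maintenance + 1000 IU | Yes |
| Running | 80%, 100%, 120% | AT continues | Maintenance | Yes |
| Running | 130% | Hold | Not addressed | Yes |
| On hold | 70%, 79% | AT restarted | Maintenance + 1000 IU | Yes |
| On hold | 80%, 100%, 120% | **No AT** | **Maintenance** | **No** |
| On hold | 130% | Hold continues | Not addressed | Yes |

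Only one row conflicts. It covers the whole 80–120% band, because nothing in either text distinguishes one part of the band from another.

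**Worked case.** A patient is held at 130% and measures 100% the next day. The Methods rule withholds AT, because 100% is not below 80%. The Discussion rule gives a maintenance dose, because 100% lies in the band. Both cannot be carried out.

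**Methods rule against the Methods aim.** The aim is a level of 80–120%. The restart trigger is a level below 80%, which is outside that range, and it is detected by a once-daily test. So if a hold ends in resumption, a value below target has been measured first. Under the Discussion wording this does not follow. It is a consequence of the wording that the investigators should know of when they reconcile the texts, and not an argument for either rule.

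**The case against.** **The Methods text is the specific rule and the Discussion text is background.** The Discussion passage explains how the dose tiers were built and says nothing about levels above 120%. One could therefore read it as describing patients who are already being infused, with the Methods supplying the stop and restart rule. On that reading the two join into one coherent scheme. This is the strongest reply and it narrows the point. It does not remove it: the Discussion passage is worded as what patients will be given, bases adjustment on weight and daily level alone, and states no exception. The reader has to supply the exception.

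**Fig. 3 or the full protocol may settle it.** This is possible. The figure could not be read here, and the article condenses a longer protocol. Either may show which rule operates at the bedside. Neither would make the two published texts agree.

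**The comparison between arms is protected.** Randomization is blocked by center and analysis is by intention to treat, so different readings in different centers would not in themselves bias the comparison. That stands. What is affected is the definition of the regimen being compared.

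**Stronger readings that a reader might infer, and why they fail**

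- *Every hold forces a value below 80%.* It does not. Supplementation stops when ECMO is discontinued, and participation can end early through death or heparin-induced thrombocytopenia (Stopping rules). A hold can therefore end with the level never having fallen below 80%. The statement is true only of holds that end in resumption.
- *A calculable fraction of daily values must fall below target.* Any such fraction needs the length of a hold-and-resume cycle. The documents give no AT decay rate, hold frequency or cycle length.
- *Centers are giving different treatment.* The 23 randomized patients reported (11 intervention, 12 control) were all in the coordinating center (Trial status), so divergence between centers is not shown.

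**Conclusion.** The point holds in a limited form. For an intervention-arm patient held above 120% whose next daily level is 80–120%, the Methods withhold AT and the Discussion, as worded, gives a maintenance dose. Elsewhere the texts are compatible. In addition, under the Methods wording, resumption follows only a measured level below the stated target.

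The size cannot be given. It depends on how many patients exceed 120% and how long they then spend in the 80–120% band, and the documents report neither. The effect on heparin dose is likewise unknown and could be nil if few patients are ever held. A material loss of AT separation between the arms is not shown: a held patient at 80–120% is still at target, while controls receive AT only with heparin resistance and a level of 50% or lower.

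The conclusion rests on reading both texts as written and on Fig. 3 being unavailable here. It calls for clarification of the tested regimen; it does not show that the trial's comparison is invalid. No view is taken on which dosing rule is right.

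**What to change.** 1. Reconcile the Methods section on the AT supplementation group, the Discussion section on developing the AT protocol, and Fig. 3 into one statement of what happens after a hold when the daily level is 80–120%. The investigators decide which rule applies.
2. Send that statement to all participating centers.
3. Summarise, by arm, the share of daily AT values within 80–120%, so that readers can see the exposure actually achieved.

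The cost is a protocol clarification, a note to centers and one descriptive table. AT activity is already recorded every day (Data collection), so no new measurement is needed, and neither the sample size nor the primary analysis changes. Control-arm rescue borrows the same supplementation algorithm with its own aim of a level above 50% (Control group), so the clarification should also say whether it applies there.

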**Fig. 3 Fig3:**
[figure not shown]
Protocol for anthithrombin supplementation

#### Control group

Patients randomized to the control group will not receive supplementation of AT unless heparin resistance occurs. The following safety criteria will be applied to define “heparin resistance”: when a patient in the control group requires more than 35 IU/kg/h of heparin and his/her AT plasma level is equal to or lower than 50%. Dosage regimen for AT supplementation in the control group will follow the same supplementation algorithm as in the treatment group. AT will be supplemented to achieve an AT plasma level higher than 50%. The AT level will be measured prior to ECMO start and then once daily.

#### Anticoagulation protocol for both groups

In both study groups, anticoagulation during ECMO will be provided with unfractionated heparin following the institutional protocol of the coordinating center, as previously published [10] (Fig. 4). Briefly, a heparin bolus of 50–70 IU/kg, depending on baseline activated partial thromboplastin time (aPTT) value, will be administered at ECMO start, followed by 18 IU/kg/h continuous infusion. For the first 12 h after ECMO start, anticoagulation will be monitored with activated clotting time (ACT) (therapeutic range 180–210 s, performed every 1 or 2 h according to the standardized protocol). From the 13th hour on, anticoagulation will be guided by aPTT, with a target aPTT ratio (patient-to-normal) range of 1.5–2.0. The frequency of aPTT measurements may vary from a minimum of three times per day to a maximum of six depending on the standardized protocol. When the aPTT value falls well below the desired range, a bolus of heparin will be administered. When the value is too high, infusion will be stopped for either 30 or 60 min. In both groups the following safety criteria will be used: in case of major surgery, during the first 24 h after operation, minimal levels of anticoagulation will be allowed to minimize the risk of bleeding. In case of minor bleeding (i.e., dripping from the site of the vascular catheter’s cannulation), physicians shall maintain anticoagulation targeted to the lower level (i.e., aPTT ratio 1.5). In case of clinically significant bleeding, heparin infusion may be interrupted until bleeding ceases; infusion will be restored starting at 50–70% of the pre-existing dose. No changes will be made to the AT dosage regimen.

**Fig. 4 Fig4:**
[figure not shown]
Anticoagulation protocol

#### Criteria for transfusions of blood products and replacement of the ECMO circuit

For the entire duration of the study, hemoglobin will be maintained at > 10 g/dL, platelet count > 50,000/mm^3^, and fibrinogen > 150 mg/dL, through packed red blood cells, platelets, and fresh frozen plasma and/or fibrinogen concentrate transfusions, respectively.

To standardize the clinical decision to replace the ECMO circuit with a new one, an ad hoc “circuit change-out score” was developed that considers the performance of the oxygenator, signs of coagulation activation by the extracorporeal circuit (e.g., drop in platelet count, increase in D-dimer level, and decrease in fibrinogen level), and the presence of hemolysis. The “circuit change-out score” includes two different conditions (A and B) defined by different sets of criteria. Condition A requires all the following three criteria to be satisfied: decrease in platelet count greater than 50% in 48 h; decrease in fibrinogen level greater than 33% in 48 h; increase in D-dimer level greater than 100% with D-dimer level higher than 30,000 ng/mL. Condition B requires two of the following three criteria to be satisfied: platelet count lower than 50,000/mL; fibrinogen lower than 150 mg/dL; D-dimer higher than 50,000 ng/mL, provided that D-dimer elevation is one of the two “B” conditions.

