#### Secondary endpoints

Adequacy of anticoagulation will be assessed through anti-factor Xa levels.

The study will also provide a preliminary evaluation of the safety of AT supplementation by comparing the incidence of the following adverse events in the two study groups: bleeding complications, classified according to a modified version of the Bleeding Academic Research Consortium score to our clinical settings [11, 12]; blood products transfusion requirements; patient’s or circuit thrombosis.

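### The platelet limit in condition B of the circuit change-out score is 1,000-fold below the platelet limit in the same section's transfusion rule, and two domains the score is said to cover have no printed criterion

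*Protocol article*

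**What the plan says.** Everything at issue stands in one section of the protocol article, *Criteria for transfusions of blood products and replacement of the ECMO circuit*.

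- **Transfusion rule (first paragraph).** Blood products are given to hold "platelet count > 50,000/mm^3^, and fibrinogen > 150 mg/dL", alongside a hemoglobin target.
- **Purpose and scope of the score (second paragraph).** The score is meant to make the decision to replace the circuit uniform. It is described as one that "considers the performance of the oxygenator, signs of coagulation activation by the extracorporeal circuit" and hemolysis.
- **Condition A.** All three are needed: a platelet fall of more than 50% in 48 h, a fibrinogen fall of more than 33% in 48 h, and a D-dimer rise of more than 100% to above 30,000 ng/mL.
- **Condition B.** Two of three are needed from "platelet count lower than 50,000/mL; fibrinogen lower than 150 mg/dL; D-dimer higher than 50,000 ng/mL". A proviso makes the D-dimer item compulsory.

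The section *Data collection* has oxygenator function and hemolysis indexes recorded daily but does not tie them to the score. The section *Study strengths and limitations* lists the replacement criteria among the strengths and presents them as criteria for considering a replacement.

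**The concern.** Two limits for the same laboratory value, one paragraph apart, carry the same figure with different volume units. One is a transfusion target and the other a trigger for circuit replacement, so this is an operative threshold and not background text. A centre that applies condition B as printed would use a different rule from one that silently reads it in the unit of the transfusion sentence. A score written to make centres act alike should not leave that open, particularly in a trial whose limitations section concedes that the intervention cannot be blinded.

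The description of the score also promises more than the list delivers. A reader told that oxygenator performance and hemolysis enter the decision finds no criterion for either and cannot tell whether they count.

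**Working it through.** **Inputs**, all from the section named above:

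| Item | Transfusion rule | Condition B |
|---|---|---|
| Platelets (P) | above 50,000/mm³ | below 50,000/mL |
| Fibrinogen (F) | above 150 mg/dL | below 150 mg/dL |
| D-dimer (D) | none | above 50,000 ng/mL, mandatory |

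**Step 1: one unit.** 1 mL = 1,000 mm³.

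- Condition B limit: 50,000/mL ÷ 1,000 = 50/mm³.
- Transfusion limit: 50,000/mm³ × 1,000 = 50,000,000/mL.
- Ratio: 50,000 ÷ 50 = 1,000.

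The two platelet limits therefore differ by exactly 1,000-fold as printed. The fibrinogen limits coincide, and D-dimer has no transfusion counterpart.

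**Step 2: what condition B becomes.** At least two of three items with D mandatory means B = D and (P or F). Without D, B is never met. With D present:

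| P | F | B with a working platelet item | B if the platelet item never fires |
|---|---|---|---|
| no | no | not met | not met |
| no | yes | met | met |
| yes | no | **met** | **not met** |
| yes | yes | met | met |

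One pattern changes: low platelets and high D-dimer with fibrinogen not below its limit. Otherwise condition B works unchanged, through D-dimer plus fibrinogen.

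**Step 3: condition A.** Its platelet and fibrinogen items are percentage falls, so no platelet unit enters and the conflict does not touch it.

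**Step 4: described domains against listed criteria.**

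| Domain named for the score | Criterion in A | Criterion in B |
|---|---|---|
| Oxygenator performance | none | none |
| Coagulation activation | platelets, fibrinogen, D-dimer | platelets, fibrinogen, D-dimer |
| Hemolysis | none | none |

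Two of the three named domains have no printed criterion.

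**The case against.** The strongest reply is that the unit is a typing slip which no clinician would follow: a count of 50/mm³ is not a believable trigger, and another unit stands one paragraph earlier. That is plausible, and the factor of 1,000 measures a conflict in notation, not an effect on the trial. But the document does not say which unit was meant, and a threshold should not depend on the reader's guess.

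On the missing domains, the reply is that a journal article condenses a longer protocol, and that saying the score includes A and B does not say it holds nothing else. Further items may sit in the full document. This makes the second part weaker than the first; what remains is that the description and the list, as printed, do not match.

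Four stronger readings are tempting, and the document does not support them:

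- **That the score cannot standardise circuit changes.** Condition A is fully specified, and condition B stays evaluable through D-dimer plus fibrinogen.
- **That limits shared with the transfusion rule are themselves an error.** One low value can both prompt a transfusion and count toward condition B. The platelet limits are in any case not shared as printed; they would coincide only if both were in the same unit.
- **That transfusion keeps patients above the limits, so condition B is out of reach.** *Study strengths and limitations* calls transfusion a clinical decision with recommended targets, and no frequency data are given. Transfusion may mask a condition B item, but nothing shows how often.
- **That the more heavily transfused arm will show fewer circuit failures.** The safety comparison covers "blood products transfusion requirements; patient’s or circuit thrombosis", and the article nowhere defines circuit thrombosis by the score.

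**Conclusion.** The point holds in a limited form. The section contradicts itself by exactly 1,000-fold on the platelet limit. Read literally, this removes one of the three patterns that would satisfy condition B and leaves condition A intact. That the platelet item would then almost never be met is an assumption: it rests on 50/mm³ lying 1,000 times below the level that transfusion aims to hold, not on data in the document.

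The mismatch between the described domains and the listed criteria is real but secondary, given that the full protocol is not shown.

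The primary endpoint (heparin in IU/kg/h) and the sample size of 40 do not use the score and are unaffected. The relevance is to uniform handling of circuit replacement across centres.

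**What to change.** Reconcile the section in three places:

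1. Use one platelet unit throughout, with the investigators confirming which limit condition B is meant to carry. Since *Trial status* says that recruitment is under way, they should also state how the limit has been read so far.
2. Align the description with the criteria: either show how oxygenator performance and hemolysis enter the score, or describe the score by the items it contains.
3. Clarify how the score relates to the transfusion limits, given that the fibrinogen limits coincide and that the platelet limits would too if both were in the same unit.

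The limits and the way they are applied are for the investigators; none is proposed here. The cost is a wording correction. Daily blood counts, coagulation values, hemolysis indexes, oxygenator function and transfusions are already collected under *Data collection*, so no new measurement is needed.
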